### Study population

#### Source cohort

All participants in the WTC-HP (*n =* 14,976) were screened, Fig. 2. *Inclusion Criteria:* i. Actively consented and enrolled member of the WTC-HP. ii. Pre-9/11 spirometry with Forced Expiratory Volume in 1 s (FEV_1_) ≥ Lower Limit of Normal (LLN) iii. Male Firefighter status on 9/11 with exposure at the WTC-site and entry into WTC-HP before the site closure on 7/24/2002. *Exclusion Criteria:* i. lung disease prior to 9/11 as defined by positive methacholine or bronchodilator test, or FEV_1_ < LLN. ii. Not part of initial cohort in data extraction from August 1, 2017 [72]. After all inclusion/exclusion criteria applied, the baseline cohort consists of *n =* 4,192. *Sub-cohort Development.* A representative cohort of 20% was randomly selected (*n =* 837; SPSS v. 28) from the above baseline cohort, Fig. 2.

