### Outcomes

Levels of salivary pepsin, pH Levels from EBC, Histamine Concentration from EBC, Score on PAGI-QOL Questionnaire, Score on PAGI-SYM Questionnaire, Score on SGRQ-C Questionnaire, and SF-36.

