### Power analysis

A sample size of 40 cases for each group of GERD, AHR, AHR/GERD overlap, BE, and non-GERD/non-AHR Controls (all will be subsets of AIM 1 *N =* 898 randomly selected cohort) achieves 80% power to detect difference as small as 0.78 SD with two-sample t-test at 0.01 significance level to account for multiple comparisons. This will allow us to achieve 80% power and significance of 0.05, based on prior studies with salivary pepsin test (personal communication with [name] of Peptest), Fig. 2.

*Statistical Analysis* SPSS 28 (IBM) will facilitate database management and statistics. Continuous variables expressed as mean, standard deviation (SD) if normally distributed, and as median, inter-quartile range (IQR) if skewed. Two-sample t-test and ANOVA will compare continuous data. Count and proportions will summarize categorical data and Pearson- χ^2^ will compare categorical data. Multivariate binary logistic regression will estimate biomarker-disease relationship for case status as a binary outcome while adjusting for confounding. Cox proportional hazards model will evaluate the effects of biomarkers, smoking, and exposure on the hazard of developing WTC-GERD or BE over time. The maximum potential effectiveness of a biomarker will be calculated by Youden Index [100]. Goodness of fit, using the Hosmer–Lemeshow test. Survival curves compared by Log-rank test. Pearson χ^2^-test will compare SABA and LABA usage between GERD, AHR, AHR/GERD overlap, BE, and non-GERD or AHR controls. Significance will be assessed by *p <* 0.05 for all statistical tests. Graphs will be created using Prism (v.10, GraphPad Software).

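### The sample size is justified at a 0.01 level chosen for multiple comparisons, but the stated analysis rule is p<0.05 for every test with no adjustment, so the correction is not carried into the analysis as written

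*Protocol article*

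**What the plan says.** All the statements about significance level are in the Power analysis section and the Statistical Analysis paragraph within it.

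- **Sizing.** Forty per group, for GERD, AHR, AHR/GERD overlap, BE and controls with neither condition, "achieves 80% power to detect difference as small as 0.78 SD" using a "two-sample t-test at 0.01 significance level to account for multiple comparisons".
- **Next sentence.** "This will allow us to achieve 80% power and significance of 0.05", with a reference to earlier salivary pepsin work.
- **Analysis rule.** Continuous data are compared by two-sample t-test and ANOVA, and significance means p below "0.05 for all statistical tests". The article names no adjusted p-values, testing order, gate or post-hoc correction.

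The sizing sentence also draws the groups from an "898 randomly selected cohort) achieves 80% power" pool. Under Source cohort, however, "A representative cohort of 20% was randomly selected" from 4,192, giving 837, and the Abstract also gives 837.

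**The concern.** The plan recognises that several groups will be compared and pays for it: the 0.01 level raises the sample size needed for a given difference. The analysis rule then returns to 0.05 for each test. If it is followed literally, the participants recruited to support a stricter threshold are analysed at a looser one, and the error control that the sizing sentence promises is absent.

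At stake is how a nominally significant group difference should be read. The Discussion says the work will validate biomarkers, so a reader would take a reported p<0.05 as protected at the level the power statement implies. Under the stated rule it is not.

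**Working it through.** **Inputs.** From the Power analysis section: 40 per group, five groups, difference 0.78 SD, level 0.01, power 80%. From the Statistical Analysis paragraph: level 0.05 per test. Sidedness is not stated. Two-sided is assumed because it reproduces the plan's figure (one-sided 0.01 would give 86.5%).

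**1. Reproduce the stated power.** For a two-sample t-test with n per group, the noncentrality is d × √(n/2) = 0.78 × √20 = 3.49, with 2 × 40 − 2 = 78 degrees of freedom. At two-sided 0.01 the critical value is 2.640 and power is 79.9%. The stated 80% is confirmed, and 0.01 is the level that generated it.

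**2. Same 40 per group at other levels.**

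| Two-sided level per test | Power at 0.78 SD | Difference detectable with 80% power |
|---|---|---|
| 0.05 | 93.1% | 0.63 SD |
| 0.0125 (= 0.05/4) | 82.1% | 0.76 SD |
| 0.01 (= 0.05/5) | 79.9% | 0.78 SD |
| 0.005 (= 0.05/10) | 72.3% | 0.84 SD |

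The sizing and the analysis rule therefore describe two different tests.

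**3. Family-wise error for one outcome.** Five groups give four comparisons with control, or 5 × 4 / 2 = 10 pairs. The document does not say which is intended. If the tests were independent, the chance of at least one false positive at 0.05 would be 1 − 0.95⁴ = 18.5% or 1 − 0.95¹⁰ = 40.1%. Comparisons that share a group are correlated, so the better figure comes from simulating five groups of 40 with no true differences and counting runs with any p-value below the threshold:

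| Level per test | 4 comparisons with control | All 10 pairs |
|---|---|---|
| 0.05, as the analysis rule reads | about 16% | about 29% |
| 0.01, as in the sizing | about 3.4% | about 7.4% |

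At 0.01, the four-comparison family is controlled below 5% (Bonferroni bound 4 × 0.01 = 4%). The ten-pair family is not (bound 10%, simulated 7.4%).

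**4. Pool size, a separate check.** 837/4,192 = 20.0%, which matches the stated 20%. 898/4,192 = 21.4%, which does not. The pool size does not enter the formula in step 1.

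**The case against.** The strongest defence is that 0.01 is 0.05/5. On that reading 0.01 is the per-test level, and the sentence about 0.05 gives the overall level. This is plausible, and it is why that sentence should be clarified rather than removed; it is also the only sentence that ties salivary pepsin to the sample size. But the defence does not reach the analysis rule, which applies 0.05 to every test and mentions no adjusted p-values.

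A second defence is that ANOVA is listed beside the t-test. If ANOVA had to be significant first, the error when no group differs would be at most 5% per outcome. The article does not say that ANOVA acts as a gate, so this lowers the figures only under an added assumption. An unseen analysis plan might also specify a correction, but the present article states a definite rule that conflicts with its own sizing.

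Several stronger readings are tempting and not supported:

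- A reader might infer that 0.01 fits no family in the design. In fact it controls the four comparisons with control.
- A reader might infer that the seven measures under Outcomes, which begin "Levels of salivary pepsin, pH Levels from EBC, Histamine Concentration from EBC", have equal standing, and multiply the error across them to about 69% (four comparisons each) or 91% (ten pairs each). Table 3, which lists the endpoints, is not shown and may rank them. Those figures also assume independent outcomes and ungated t-tests, although four of the seven are questionnaire scores from the same participants.
- A reader might infer that the study is underpowered. At 0.05, power at 0.78 SD rises to 93.1%.
- A reader might link 898 versus 837 to the loss of error control, or to sampling weights. The pool size has no bearing on alpha, and the article describes no weighted analysis. Figure 2, not shown, might explain 898.

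**Conclusion.** The contradiction is real and lies within one section: the sample size rests on 0.01 per test because of multiplicity, and the analysis rule is 0.05 per test with no adjustment. As written here, the correction is not carried forward. This does not establish that no correction exists in any other document.

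For a single outcome the family-wise error under the written rule is about 16% or 29%, depending on whether four or ten comparisons are made, against about 3.4% or 7.4% at the sizing level. These figures assume two-sided t-tests, equal groups of 40, normal data, no true differences and no ANOVA gate. The sample-size calculation itself is correct. The mismatch between 898 and 837 is a separate, smaller inconsistency.

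**What to change.** 1. Clarify that 0.05 is the overall level, keep the link to salivary pepsin, and state the family of group comparisons it covers.
2. Replace the blanket p<0.05 rule with the matching rule for that family.
   - Four disease groups against control: keep the planned 0.01 per test (79.9% power at 0.78 SD), or use 0.0125 (82.1%). Both control the error with 40 per group.
   - All ten pairs: use 0.005, restate the detectable difference as 0.84 SD, and acknowledge 72.3% power at 0.78 SD.
3. If ANOVA is meant to gate the pairwise tests, say so.
4. Label the remaining outcomes exploratory, or adjust them for multiplicity, consistently with the ranking in Table 3.
5. Separately, reconcile 898 in the Power analysis section with 837 in the Abstract and Source cohort, or explain the difference.

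The cost is wording only, with no added participants. Some differences that would have been reported as significant at 0.05 will no longer be.

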### Salivary pepsin assessment

30 mL sterile plastic tubes with 0.5 ml of 0.01 M citric acid, adjusted to a pH of 2.5 (RD Biomed Ltd., Hull, UK), will be used by the participants to collect saliva in the AM (prior to brushing teeth, drinking or eating), 1 h after finishing lunch, and 1 h after finishing dinner [78, 79]. Participants will be instructed to cough a few times prior to spitting into the tube to clear saliva from the back of the throat and then spit into the tube. The collected samples will be stored at 4 °C and analyzed within 2 days. Salivary Pepsin will be analyzed using Peptest (RD Biomed Ltd., Hull, UK) as previously described [79]. Briefly, plastic tubes will be centrifuged at 4,000 rpm for 5 min, and 80μL of supernatant will be added to 240μL of migration butter solution for 10 s. 80μL of the mixture will be added to the well of the Peptest, which contains two unique human monoclonal antibodies that detect and capture pepsin protein (specific to pepsin-3), with a lower limit of detection of 16 ng/mL and an upper limit of 500 ng/mL. A salivary pepsin level of ≥ 16 ng/mL will be considered positive. The sample will be processed in a Pepcube reader to quantify the pepsin concentration [78].

*Spirometry* will be assessed using a KoKo PFT spirometer (nSpire Health Inc)**,** and lung function assessment will be considered acceptable as per the ATS/ERS guidelines [80]. We will select the largest acceptable measures for electronic archiving. Each participant’s predicted percentage (%) will be calculated by NHANES III equations based on their age at examination, height, sex, and race [80, 81].

*FeNO* will be quantified using NIOX VERO® (Aerocrine) [82, 83]. Participants will be instructed to inhale to their total lung capacity via mouthpiece for 2–3 s. Then, they will exhale at a flow rate of 0.05L/second. The device will provide results in parts per billion (ppb).

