### Microbiome of the gut/lung axis

Asthma susceptibility is influenced by the gut microbiome [106–111]. Noninvasive collection sites that can approximate the pulmonary environment are of key interest. Studies have failed to show that the microbiomes of induced sputum were similar to the lung [112, 113]. Noninvasively collected oropharyngeal and nasopharyngeal swabs in conjunction could approximate the lung microbiome [114]. Research has revealed that the esophageal microbiome undergoes alteration in individuals with GERD, BE, and other motility disorders [115, 116]. Although these findings highlight the potential role of the microbiome studies in the diagnosis and therapeutic approaches for aerodigestive disease, further studies are needed and will be one of the key readouts planned in our study.

*EBC* analysis holds great promise in addressing unmet medical needs by expanding the portfolio of noninvasive assays for the multiple coexisting pathological mechanisms underlying respiratory disorders and GERD. Compounds identified in EBC include histamine, adenosine, ammonia, hydrogen peroxide, isoprostanes, leukotrienes, nitrogen oxides (NOx), peptides, cytokines, protons and various ions [85]. Histamine plays a vital role in digestion but elevated levels can contribute to the development of GERD [117, 118].

*Salivary pepsin* has been studied in several GERD biomarker studies [105]. Due to the overlap of various reflux symptoms with other GI pathologies, the diagnosis of GERD can be challenging. However, salivary pepsin test offers a simple and convenient way for detecting reflux through salivary sample collection, providing quick and non-invasive results. Compared to other diagnostic modalities, this approach is time-efficient and requires much less effort [119]. Moreover, pepsin measurements can identify pathologic reflux even in the absence of symptoms, and remain unaffected by the concurrent use of PPI. Several studies have demonstrated that pepsin detection in the sputum and/or saliva can be regarded as a sensitive, non-invasive method for the diagnosis of the proximal reflux of gastric contents, with a sensitivity ranged from 41.5% to 73% and high specificity of 86.2 to 98.2% [78, 79]. Despite these findings little is known about pepsin in the context of aerodigestive co-morbid disease.

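### Salivary pepsin, the only outcome named in the sizing, is likely to be mostly below detection in controls, yet levels are to be compared by t-test/ANOVA and the 80% power is not tied to a pepsin distribution

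*Protocol article*

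**What the plan says.** All references are to the protocol article.

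- **Power analysis.** "A sample size of 40 cases for each group of GERD, AHR, AHR/GERD overlap, BE, and non-GERD/non-AHR Controls" "achieves 80% power to detect difference as small as 0.78 SD with two-sample t-test at 0.01 significance level to account for multiple comparisons". The basis given is "based on prior studies with salivary pepsin test". No pepsin mean, SD, measurement scale or detection rate is reported.
- **Statistical Analysis** (a paragraph within the Power analysis section). Continuous variables are summarised by mean and SD if normal and "as median, inter-quartile range (IQR) if skewed". The comparison is then the same for all of them: "Two-sample t-test and ANOVA will compare continuous data". Pearson chi-square is named for categorical data and logistic regression for case status. The 0.05 level applies "for all statistical tests".
- **Outcomes.** Salivary pepsin level is listed first.
- **Salivary pepsin assessment.** The assay works "with a lower limit of detection of 16 ng/mL and an upper limit of 500 ng/mL", and a result is positive from 16 ng/mL upwards. Three samples are collected per participant.
- **Discussion**, salivary pepsin paragraph (under the heading on the microbiome of the gut/lung axis). Earlier studies found pepsin to be diagnostic "with a sensitivity ranged from 41.5% to 73% and high specificity of 86.2 to 98.2" per cent.

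**The concern.** The plan recognises skewness when it describes data and ignores it when it tests them. For pepsin the mismatch goes beyond skewness. Because the detection floor and the positivity cut coincide, every negative result is a value known only to be below 16 ng/mL. A group with high specificity is then a block of identical non-detects plus a few positive readings. A mean difference in SD units describes such data poorly, and a few high readings drive the t-test.

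Two things are at stake. One is efficiency on the marker used to size the study: a real difference could be missed with a t-test that a rank test would have found. The other is dependence on an arbitrary choice. A t-test needs a number for each non-detect, and the result moves with that number. A rank test treats all non-detects as tied at the bottom, whatever number is entered for them.

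**Working it through.** **1. Reproducing the stated power.** Inputs: n = 40 per group, d = 0.78, alpha = 0.01, taken as two-sided. The noncentrality is d × √(n/2) = 0.78 × √20 = 3.49, with 78 degrees of freedom and a critical t of 2.64. The exact noncentral-t calculation gives 79.9%, so the 80% is right on its own terms.

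**2. Expected non-detects.** Assume the Discussion's accuracy figures hold at 16 ng/mL and for a single sample.

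- Controls: 0.862 × 40 = 34.5 to 0.982 × 40 = 39.3, so about 34–39 of 40.
- GERD cases: (1 − 0.73) × 40 = 10.8 to (1 − 0.415) × 40 = 23.4, so about 11–23 of 40.

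**3. t-test against rank test.** The documents give no distribution, so one is assumed: log-normal levels with the same log-SD σ in both groups, σ from 1 to 2. To give a fraction p at or above 16 ng/mL, the log-mean is ln 16 + σ × Φ⁻¹(p). Values below 16 are set to 0 and values above 500 to 500. Simulated power, 40 per group, alpha 0.01:

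| Sensitivity / specificity | t-test | Mann-Whitney |
|---|---|---|
| 41.5% / 86.2% | about 31–51% | about 63% |
| 41.5% / 98.2% | about 72–94% | about 99% |
| 73% / 86.2% | about 99% | about 100% |
| 73% / 98.2% | about 100% | about 100% |

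Repeat runs differ by a few points (28–52% for the first t-test entry). With σ from 0.8 to 1.6 instead, the t-test gives 30–58% in the first row and 74–98% in the second.

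**4. Effect of the substituted value.** At σ = 1, t-test power changes as follows when non-detects are entered as 0, 8 or 16:

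- 41.5% / 86.2%: about 52%, 43% and 28%.
- 41.5% / 98.2%: about 94%, 87% and 68%.

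The rank test does not change, because the ordering is the same.

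**5. Positive against negative.** Exact power of Pearson chi-square, 40 per group, single-sample positivity:

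- 41.5% v 13.8%: 60.9% at alpha 0.01 and 81.2% at 0.05.
- 41.5% v 1.8%: 99.3% at 0.01.
- 73% v 13.8%: 99.9% at 0.01.

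The definition of positivity matters. Suppose the rates are per sample, the three samples are independent, and any positive counts. Positivity then becomes 1 − 0.585³ = 80% against 1 − 0.862³ = 36%, and power at 0.01 is 94%.

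**6. What 0.78 SD could mean.** If it is the difference on the measured, censored scale, t-test power in the same kind of model (σ 0.8–1.6, control positivity 1.8–30%) is 87–98%. If it is a difference on the uncensored log scale, t-test power is 1–65% for control positivity from 1.8% to 50%, and the rank test reaches only 4–73%. The article does not say which scale is meant.

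**The case against.** A reader might infer that the stated 80% power is simply not delivered. The documents do not support that, for these reasons.

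- The claim is conditional on a 0.78 SD difference and reproduces. Censoring alone does not break it (step 6, measured scale).
- The low-power corner is a smaller effect, about 0.46–0.55 SD after censoring. On normal data a t-test at 0.01 has about 30% power at 0.47 SD and 43% at 0.55 SD, so low power there does not contradict a claim about 0.78 SD. Rank and positivity tests also miss 80% at that corner.
- The Discussion gives two ranges. It does not pair the lowest sensitivity with the lowest specificity, and at 73% sensitivity the choice of test hardly matters.
- The detection rates are inferred. The accuracy figures cover sputum and/or saliva, with no stated cut-off. Controls here are defined from records and medication, and the limitations section expects that some people without a GERD history may have raised pepsin.
- At the 0.05 level used in the analysis the shortfall is smaller: the t-test has 65–78% at the worst corner and at least 97% elsewhere.

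Two further limits apply. The 500 ng/mL ceiling matters little: at 41.5% sensitivity at most about 3% of cases reach it, and at 73% sensitivity, where more do, power remains ample. The t-test's type I error was at or below its nominal level in simulation, so validity is not in question.

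It can also be said that chi-square and logistic regression are already planned, and that an article may leave non-detect rules to a fuller document. That is fair for the substitution rule. It does not answer the main point, because the article positively assigns t-test and ANOVA to continuous data, including data it would summarise by medians.

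**Conclusion.** The point holds as one of test choice and unsupported power, not of demonstrated power failure. The test named for pepsin levels does not suit an outcome likely to be dominated by non-detects. At 41.5% sensitivity it costs roughly 12–32 percentage points of power against a rank test at 86.2% specificity (63 − 51 to 63 − 31), and 5–27 points at 98.2% (99 − 94 to 99 − 72). At 73% sensitivity the cost is negligible. The t-test result also depends on an arbitrary substituted value.

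The 80% for 0.78 SD is correct arithmetic, but it is not linked to any pepsin distribution and so is not assured for pepsin over the article's own accuracy range.

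These sizes rest on log-normal levels with log-SD 1–2, alpha 0.01, non-detects set to 0, and the Discussion's accuracy figures applying at 16 ng/mL. The mismatch between summary and test rests on none of these. The change should be made before analysis.

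**What to change.** 1. Compare pepsin levels by Wilcoxon (pairwise) and Kruskal-Wallis (across the five groups), with non-detects as ties at the floor. A Tobit or two-part model is an alternative.
2. Use rank tests or a log scale for other markers that prove skewed.
3. Keep positivity at 16 ng/mL or above, by chi-square and logistic regression, as a companion analysis. Say whether it means a single sample or any of the three.
4. State the scale and the pepsin data behind 0.78 SD. Report pepsin power as a range over the assumed detection rates, computed for the same positivity definition that is analysed.

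The cost is a few sentences of analysis wording, with no new participants or samples. The drawback is a less favourable power figure at the low end: about 61% at alpha 0.01 for 41.5% v 13.8% positive on a single-sample definition.

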**Methods:**

Our observational case-cohort study will leverage the longitudinally phenotyped Fire Department of New York (FDNY)-WTC exposed cohort to identify *Biomarkers of Airway Disease, Barrett’s and Underdiagnosed Reflux Noninvasively (BAD-BURN)*. Our study population consists of *n =* 4,192 individuals from which we have randomly selected a sub-cohort control group (*n =* 837). We will then recruit subgroups of *i.* AHR only *ii.* GERD only *iii.* BE *iv.* GERD/BE and AHR overlap or *v.* No GERD or AHR, from the sub-cohort control group. We will then phenotype and examine non-invasive biomarkers of these subgroups to identify under-diagnosis and/or treatment efficacy. The findings may further contribute to the development of future biologically plausible therapies, ultimately enhance patient care and quality of life.

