**Fig. 2 Fig2:**
[figure not shown]
Study design

*Recruited Cohort* will be developed to assess for noninvasive biomarkers. We will recruit a subset *N =* 40/group (*i.* AHR only *ii.* GERD only *iii.* BE *iv.* GERD/BE and AHR overlap or *v.* No GERD nor AHR) from the sub-cohort, Fig. 2. Recruitment strategies will include: i. Direct mailings; ii. Email (potential participants will be sent the same IRB-approved recruitment message to their personal emails using end-to-end encryption; iii. Study website will include recruitment messages providing general information on the study and answers to frequently-asked questions. No direct communications will be made with participants through the website, and no PHI will be used or available within the study website; iv. Telephone contact. A description of the study will be provided to potential participants and, upon their expression of interest, the investigator will perform an eligibility screening. In addition to meeting the inclusion criteria as outlined above, participants should: i. have available serum from their first post 9/11 WTC-HP ii. Not currently be receiving treatment for malignancy iii. Have no limitations to a minimal risk blood draw iv. Be willing and able to sign consent; and v. be able to attend a single-visit.

All co-investigators have received training from the principal investigator in how to obtain consent and answer questions that may arise during the consent process. The consent and letter have been written to comply with the requirement that they be written at a 5th grade reading level, evaluated by the Flesch–Kincaid readability test. In addition, subject will be asked to provide their understanding of what the study is about at the time of the consenting process. English is the primary language of all FDNY rescue workers, see Appendix.

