### Model building

We have previously identified key biomarkers using a machine learning approach [10, 28–30]. We have further refined this analysis pipeline and will utilize this methodology to identify AHR, GERD, AHR/GERD overlap, and BE biomarkers**.** Specifically, we will utilize random forests (RF) of the filtered, normalized biomarkers. Models assessed via a modified hamming distance between variable importance rankings of models with identical hyper-parameters. A refined profile of the top 5% of important biomarkers by MDA will be included in a gradient-boosted tree model (xgboost package, R-Project) to build a classifier of AHR, GERD, AHR/GERD overlap, and BE. A random hyperparameter space search determined a final model that maximized AUC_ROC_.

We will also use linear mixed-effects models will be used to assess the temporal trend of biomarkers with time adjusting for confounders. The longitudinal biomarkers processes will be associated to risk of developing WTC-GERD/BE using the joint modeling technique [101]. The joint-modeling approach has become the primary method for analysis of longitudinal biomarker process and time-to-event outcome, and multiple R packages are available to implement the models. We will also consider a single index longitudinal model which enables us to reduce the dimensionality of multiple biomarkers and to evaluate joint effects of multiple biomarkers together to identify key risk factors. The single-index model incorporates longitudinal data to calculate hazard of each parameter as well as personalized dynamic risk for prognostication. Specifically, this will allow us to use a patient’s data from a single clinical exam to identify risk of GERD, AHR, overlap, or BE. Furthermore, this will allow the identification of false negatives and undertreated cases in the entire FDNY cohort.

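### The recruited sample is filled by disease quotas, but the GERD/BE time-to-event and risk models are named without sampling weights or recalibration before cohort-wide use

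*Protocol article*

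**What the plan says.** **Sampling.** The Source cohort section draws a random 20% sub-cohort (837 of 4,192). The Recruited Cohort paragraph then takes "40/group (*i.* AHR only *ii.* GERD only *iii.* BE *iv.* GERD/BE and AHR overlap or *v.* No GERD nor AHR) from the sub-cohort". The Power analysis section repeats the 40 per group. Case status is defined largely from the electronic medical record (EMR), endoscopy, pH studies and medication use.

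**Time-to-event analysis.** The Statistical Analysis paragraph states: "Cox proportional hazards model will evaluate the effects of biomarkers, smoking, and exposure on the hazard of developing WTC-GERD or BE over time". It adds: "Survival curves compared by Log-rank test".

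**Risk models.** Model building links longitudinal biomarkers to GERD/BE risk in a joint model. It also considers a single-index model that yields individual dynamic risk, and expects that "this will allow the identification of false negatives and undertreated cases in the entire FDNY cohort".

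**Design label.** The abstract opens its methods with "Our observational case-cohort study will leverage the longitudinally phenotyped", while the title and Discussion say case-control.

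Nowhere does the article mention sampling weights, case-cohort estimation or recalibration. It does not say which participants enter each time-to-event model.

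**The concern.** The event in the Cox, log-rank and joint models is developing GERD or BE. Those same conditions, together with AHR, decide who is recruited. Inclusion therefore depends on the outcome, and the share of events in the recruited sample is set by the quotas rather than by nature.

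Salivary pepsin, FeNO, exhaled breath condensate and microbiome data are described only for recruited participants, so any risk model that uses them has to rest on the quota sample. If standard methods are applied there without adjustment, survival curves and individual risks describe a population with an artificial case mix. A count of missed or undertreated cases in the whole cohort would inherit that error. Hazard ratios would be distorted as well, more so when a biomarker is related to AHR. That is likely for some markers, since the study seeks markers of both diseases and the Discussion describes FeNO as associated with AHR.

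**Working it through.** **1. The plan's own figure.** 40 per group, 0.78 SD, two-sample t-test, alpha 0.01 (two-sided assumed), 80% power.
- Normal approximation: n = 2 × (2.576 + 0.842)² / 0.78² = 38.4, so 39 per group.
- Exact noncentral-t power at 40 per group: 79.9%.

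The figure reproduces. It concerns group comparisons and is untouched by this point.

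**2. What the quotas fix (no assumption beyond filled quotas).** Total 5 × 40 = 200.
- GERD/BE: GERD only + BE + overlap = 120/200 = 60%.
- BE: at least 40/200 = 20%.
- AHR: AHR only + overlap = at least 80/200 = 40%.

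With common follow-up, an unweighted curve ends at these values.

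**3. Unequal sampling fractions.** For true GERD/BE frequency p, the ratio of case to non-case sampling fractions is (120/p)/(80/(1−p)) = 1.5(1−p)/p. For BE it is (40/p)/(160/(1−p)) = 0.25(1−p)/p. Neither depends on the size of the sub-cohort.

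| Assumed frequency | Ratio |
|---|---|
| GERD/BE 20% | 6.0 |
| GERD/BE 30% | 3.5 |
| GERD/BE 44% | 1.9 |
| GERD/BE 60% | 1.0 |
| BE 5% | 4.75 |
| BE 10% | 2.25 |

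The 44% is the Background figure for WTC rescue and recovery workers by 2005, not for this sub-cohort. The article gives no GERD, BE or AHR frequency for the sub-cohort, so all of these are assumptions.

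**4. Simulation of absolute risk and hazard ratio.** Sub-cohort 837, exponential event times, 20 years, up to 40 drawn per group, 200 runs per scenario. Assumed: AHR 25%, BE 6%, standard normal biomarker, true hazard ratio 2.0 per SD.

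| Assumed GERD | Quantity | Full sub-cohort | Quota sample, unweighted | Quota sample, weighted |
|---|---|---|---|---|
| 44% | GERD/BE risk | 46.7% | 60.0% | 46.7% |
| 44% | BE risk | 6.0% | 19.9% | 6.0% |
| 44% | GERD/BE HR | 1.99 | 1.88 | 2.01 |
| 44% | BE HR | 1.98 | 1.75 | 1.98 |
| 20% | GERD/BE risk | 24.2% | 59.2% | 24.2% |
| 20% | GERD/BE HR | 2.00 | 1.65 | 2.04 |
| 20% | BE HR | 2.01 | 1.55 | 2.04 |

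Weights are (number in group)/(number drawn from group).

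**5. Sensitivity of the hazard ratio.** Assumed GERD 20-45%, BE 5%, AHR 30%; frame 837 or 4,192; participants with both BE and AHR placed in either group.

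| True HR per SD | Endpoint | Biomarker unrelated to AHR | Biomarker predicts AHR (OR 2 per SD) |
|---|---|---|---|
| 1.50 | GERD/BE | about 1.33-1.45 | about 1.21-1.37 |
| 1.00 | GERD/BE | about 1.00 | about 0.93-1.00 |
| 1.00 | BE alone | about 1.00 | about 0.80-0.92 |

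For GERD/BE, weighting returns about 1.48-1.54 for a true 1.50 and 0.99-1.01 for a null. Without an AHR link the bias is near zero when GERD/BE is about 60%, because the sampling fractions are then equal: 120/502 = 80/335 = 0.24.

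**The case against.** **Silence is not a statement.** A reader might infer that the plan prescribes unweighted models. It does not. It names standard methods and says nothing on weights, and this is a condensed article whose analysis plan is not shown. That stands, so the point is conditional.

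**The analysis set may need no weights.** The Power analysis section calls the 40-per-group sets subsets of a randomly selected Aim 1 cohort, and the Limitations section says that serum was banked within six months of 9/11. Cox models on the whole random sub-cohort with banked serum would be sound without weights. Markers from a single visit long after 9/11 are also unnatural predictors of earlier incidence. This too stands. However, the article never assigns these models to the whole sub-cohort. It makes available banked serum a condition for recruited participants, and the newer markers exist only for them.

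**Is the case-cohort design misapplied?** One might infer this because all five groups come from the sub-cohort. The documents do not support it: the study design figure is not available, and the recruitment text may describe a second phase only. Nor can a shortage be shown from 40/837 = 4.8%, since no BE frequency is given.

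**Size.** It is tempting to read a spurious hazard ratio near 0.89 as the consequence for GERD/BE under the null. A value that low arises for BE alone and only with an AHR link. GERD here may also exceed 44%, since antacid use counts as GERD, and the bias then shrinks.

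**Scope.** The listed outcomes and the power statement concern group comparisons, which are not affected in the same way, and the single-index model is only under consideration.

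**Conclusion.** The point holds in conditional form. The article fixes outcome quotas, names standard time-to-event and risk models for the same outcome, and commits to cohort-wide use, with no step that links the sample back to the cohort.

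If those models are run on the recruited sample as named, the error in survival curves and absolute risks is certain unless the true frequencies happen to match the quotas. The error in hazard ratios is generally attenuation. It is modest if GERD is near 45%, larger if GERD is less common, for BE alone, or for a biomarker tied to AHR, and close to zero without an AHR link if GERD is near 60%.

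The 60% and 20% shares follow from the quotas alone. All hazard-ratio figures rest on assumed frequencies, exponential event times and random sampling within groups.

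**What to change.** 1. State the analysis set for every Cox, log-rank, joint and single-index model.
2. Where banked serum and EMR variables suffice, fit the model on the whole random sub-cohort; no weights are then needed.
3. Where the recruited sample is used, weight each participant by (eligible in stratum)/(recruited in stratum) with robust variance, and use weighted survival curves and tests. The strata must be mutually exclusive, so say where a participant with both BE and AHR is counted. The sampling frame must also be one number: the Source cohort section gives 837 and the Power analysis section 898.
4. Recalibrate any absolute risk, or any count of false negatives or undertreated cases, to the stratum sizes before applying it to the FDNY cohort.

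**Cost.** Analysis wording and a table of stratum counts obtainable from the EMR-based case definitions, with no change to recruitment. Confidence intervals will be somewhat wider. The weights do not correct for volunteer selection within strata, which should be reported as a remaining limitation.
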